## 1. INTRODUCTION

Age-related macular degeneration (AMD) is a progressive, late onset disease affecting central vision that is currently the leading cause of irreversible blindness in our community. Early signs of the disease are present in 15% of the population aged 50 years and older and by 90 years of age, more than two-thirds of the population are affected. The high prevalence of AMD, the anticipated increase in the ageing population and the very limited treatment options available highlight the urgency for further research and the implementation of a preventative strategy to retard the progression of this debilitating disease.

The pathogenesis of AMD remains largely unknown, however it is regarded as a genetic disorder where environmental risk factors impact on the genetic background. The potential environmental risk factors are numerous however, smoking is currently the only factor consistently associated with AMD. Other cardiovascular risk factors such as hypertension, atherosclerosis, high serum cholesterol and high dietary fat intake have also been linked to AMD although inconsistently.

Recently, several pieces of evidence have further implicated cholesterol in AMD pathogenesis. Firstly, came the report that the cholesterol pathway gene apolipoprotein E (APOE) may play a role in AMD and other degenerative diseases such as atherosclerosis and Alzheimer's disease. Secondly, the association of AMD with cardiovascular disease was reported in several studies.

Apolipoprotein E being a plasma lipoprotein plays a basic role in the degradation of particles rich in cholesterol and triglycerides. The polymorphic nature of the gene affects various diseases in different ways depending on which allele of the gene is present. That is, in cardiovascular disease the  $\epsilon 2$  allele is protective and the  $\epsilon 4$  allele a risk factor for disease. In AMD, the  $\epsilon 4$  allele has been shown to be protective whilst the  $\epsilon 2$  allele was significantly associated with an increased risk of AMD.

There are many postulated mechanisms by which atherosclerosis could play a part in the development of AMD. A proposed model for the development of AMD is that deficiencies in the choroidal vasculature leads to deterioration in the retinal pigment epithelium resulting from the build up of waste products. Blood flow to the choroidal vessels could be affected as well as the surface area of the choriocapillaris. The same mechanisms that cause lipids to be deposited in the walls of systemic arteries in atherosclerosis may also be involved in the deposition of lipids in crucial structures in the retina associated with AMD.

An overlap between the risk factors for cardiovascular disease and AMD have lead to the proposal that the two conditions may have a common aetiologic pathway. Components of cardiovascular disease such as hypertension and atherosclerosis have been studied in relation to AMD with inconsistent findings.

There have been several studies that have reported a significant association between hypertension and AMD. Of particular interest are the findings from the AREDS group that reported an increased risk of large soft drusen or neovascular AMD in people with

hypertension.

The Rotterdam Study was the first population-based study to report a significant association between carotid atherosclerosis determined by the presence of atherosclerotic plaques and late AMD. This was supported by the findings of *Chaine et al* in 1998 who reported a significant association between coronary heart disease and advanced forms of AMD.

Dietary fat intake may also influence the risk of developing age-related macular degeneration by raising the levels of cholesterol in the bloodstream thereby increasing the risk of atherosclerosis or alternatively, there may be an increase in the deposition of fat in Bruch's membrane that adversely affects the flow supply of nutrients and the removal of waste products from the retinal pigment epithelium^17. In recent years both the Blue Mountains Eye Study and the Beaver Dam Eye Study have shown that higher intake of specific fats associated with higher cholesterol levels were significantly associated with the presence of AMD.

Data collected from our population-based study of eye diseases (Melbourne Visual Impairment Project) was used to examine whether the progression of early AMD was delayed in people taking cholesterol-lowering medications. Our results showed for the first time, that participants on cholesterol-lowering medications were almost four times less likely to experience progression of AMD than participants who did not, although the major limitation was the small number of people who actually took such medications.

Further evidence to support our findings emerged from a survey of 379 men and women

residing in Sheffield, England. The survey found that men and women aged 66-75 who took statins had an eleventh the risk of AMD compared to those not taking the drug.

Given these findings, our aim is to assess the effect of a specific class of cholesterol-lowering medication 'statins' in reducing the progression of AMD in people with early signs of the disease. The rates of progression will be assessed in terms of APOE genotype to see if any correlation can be made.

People participating in this study will have fasting blood cholesterol levels below which are normally recommended to treat.

1. VanNewkirk M. et al      Ophthalmology                      2000; 107: 1593-1600
2. Smith W. et al              Arch Ophthalmology                  1996; 114: 1518-1523
3. Snow KK. et al              Ophthalmic Epidemiol                1999; 6: 125-143
4. Klein R. et al                Ophthalmology                        1995; 142: 404-409
5. Smith W. et al                Arch. Ophthalmol.                      1998; 116: 583-587
6. Vingerling J. et al            Am. J. Epidemiol                        1995; 142: 404-409
7. Souied E. et al                Am. J. Ophthalmol                      1998; 125: 353-359
8. Davignon J. et al              Clin Chima Acta                        1999; 286: 115-143
9. Strittmatter W. et al        Proc. Natl. Acad. Sci USA            1995; 92: 4725-4727
10. Horejsi B et al                Physiology Research                  2000; 49: S63-S69
11. Klaver C. et al                Invest. Ophthalmol &Vis. Sci        2001; 42: S310
12. Friedman E, et al              Ophthalmology                        1995; 102: 640-646.
13. Sperduto RD and Hiller R   Arch. Ophthalmol                      1986; 104: 216-219
14. Hyman L et al                Arch. Ophthalmol                      2000; 118: 351-358

## 2. STUDY RATIONALE

Age-related macular degeneration (AMD) is currently the leading cause of irreversible visual impairment in our community. Despite numerous large, multi-centred studies aimed at finding treatments or prevention for AMD, the rates of blindness associated with the disease have not significantly decreased. New treatments mostly aimed at reducing visual loss once complications have occurred have had very little impact on this disease. It is therefore likely that prevention or slowing of the progression will have an important impact on this disease until better treatment is available.

Our recent findings within the department have shown that the use of cholesterol-lowering drugs may offer the first proven intervention available for slowing the progression of AMD to the late stages where severe vision loss is experienced. We therefore commence in 2003 a randomised-controlled trial of cholesterol-lowering agents, 'statins' in people with early AMD. The APOE gene allele status of each normocholesterolaemic individual will be determined to investigate whether the APOE allele type influences who will and will not progress on this medication.

#### 4. STUDY OBJECTIVES

**The primary objective** of this study is to determine whether SIMVASTATIN at 40mg per day versus a placebo affects the progression of early AMD, either to the development of late stage AMD, defined as either CNV or central geographic atrophy, or as worsening macular status within the stage of early AMD.

**Secondary objectives** are to measure changes in visual function results over time and to determine how the genotype influences the findings on AMD progression in normocholesterolaemic participants.

##### 4.1 Endpoint

The endpoint of the study is the development of late stages AMD. If late AMD develops in both eyes, the participant exits the study and no further scheduled examinations will be required. If late AMD occurs in one eye, the fellow eye remains under observation and the follow up continues.

#### 5. STUDY DESIGN

The study is a randomised, double-masked, controlled study. The study is based at the Royal Victorian Eye and Ear Hospital and Caulfield General Medical Centre. .

Participants are being randomised in a ratio 1:1, to receive either the active 'statin' or the placebo once they have completed both the ophthalmic and cardiovascular requirements outlined in the protocol.

Participants receive the same study treatment for the duration of their involvement in the study.

## 6. PARTICIPANT POPULATION

### 6.1 Sample size

In photo-based detection, the rate of progression of early AMD in people with high- risk features was found to be 5% per year in the AREDS study. In the VIP project, AMD progression in people on cholesterol-lowering medications was 4 times lower than those not on any such medication. To detect a similar reduction in AMD progression, a sample size of 118 subjects in each arm, followed for three years, was needed to reach 80% power at a 5% level of significance.

20. McCarty et al                      MJA                      2001 175: 340

22. AREDS                      Arch Ophthalmol                      2001 119: 1417-1436

In the more sensitive functional tests, a smaller sample size would be required. Thus, a sample size of 50 patients per treatment group would be sufficient to detect a 22% to 41% change in sensitivity for the different functional methods, or it will be sufficient to detect a 3.4 min difference in rod-cone break over the trial period, with statistical power of 80% .

### 6.2 Inclusion criteria

- (1) male or female aged 50 years or older,
- (2) the ability to assess the macula in at least one eye,
- (3) VA better than or equal to 6/18 in the study eye(s).
- (4) High risk drusen in both eyes –  $\geq 1$  large soft druse (125 microns), or  $>10$  intermediate drusen (62.5 microns)

OR

Late AMD (CNV, GA) in one eye and any drusen or pigment change in the

study eye.

Note: the study eye is allowed to have non-central GA and/or non-neovascular PED

- (5) cholesterol level within the normal limits according to the person's medical history
- (6) not currently on any cholesterol-lowering medication.

### 6.3 Exclusion criteria:-

- (1) Medical and ophthalmic conditions which potentially affects visual function –  
including visually significant cataract (as defined by WILMER's grading method-that is nuclear opacity score of 2.00 or greater, cortical opacity score of greater than 3, any posterior subcapsular cataract), history of diabetes and glaucoma
- (2) Use of medications which may affect visual function, such as plaquenil, chloroquine, major tranquilizers.
- (3) cholesterol levels outside the normal limits given person's medical history.
  - Existing coronary heart disease:-- **cholesterol > 4 mmol/L**
  - Diabetics, people with hypertension, peripheral vascular disease, family history of hypercholesterolaemia or coronary heart disease:--  
**cholesterol > 6.5mmol/L or cholesterol > 5.5 if HDL <1.0mmol/L**
  - people with HDL <1.0mmol/L:--**cholesterol >6.5mmol/L**
  - men aged 35 to 75 years or postmenopausal women up to 75 years:--  
**cholesterol >7.5 or triglycerides > 4.0mmol/L**
  - people with none of the above:--**cholesterol >9.0 or triglycerides >8.0mmol/L**

(4) Statins is clinically contraindicated

- Allergy
- ALT > 2 times the upper limit of normal
- Previous severe adverse reactions to statin

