### **Instruction**

Take two tablets in the evening with food. Avoid drinking grapefruit juice within 4 hours of taking the medication as this may interfere with absorption.

Severe side effects are rare, but seek medical advice promptly if you experience muscle pain, tenderness or weakness, dark urine, or yellowing of skin or the whites of your eyes.

**Please give the enclosed “information for GP” to your local doctor. Please remind him/her that you are now in this trial, especially when he is about to prescribe any drug (particularly antibiotics), as there are a few but important interactions.**

Please call [name] on [name], or [name] on [name] if you have any questions regarding the medication or the trial.

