## APPENDIX 9: Letter to GP on commencing medication

Dear doctor,

Your patient has been enrolled into the Age-Related Maculopathy Statins Study (ARMSS). This study looks at whether statin impacts on the rate of progression of age-related maculopathy (ARM). 50% of participants will be randomized to receive simvastatin 40mg, and 50% will be on an identical looking placebo.

Please be aware that simvastatin can have the following interactions drug interactions:

- Bile acid binding resins – reduce gastrointestinal absorption of statin. Give statin at least one hour before, or 4 hours after, bile acid binding resin.
- Clarithromycin, itraconazole, ketoconazole, erythromycin – increase risk of myopathy or rhabdomyolysis – stop statin temporarily, for the duration of antimicrobial treatment.
- Cyclosporin – increases risk of myopathy or rhabdomyolysis; use lowest effective statin dose, monitor for adverse effects, and measure creatinine kinase if indicated.
- Gemfibrozil – increases risk of myopathy and rhabdomyolysis; measure creatinine kinase 1 month after starting combined treatment with statin, then repeat at 6 month intervals and if symptoms of myopathy or rhabdomyolysis occur.
- Nicotinic acid (lipid lowering doses) – increases risk of myopathy and rhabdomyolysis; monitor clinically; measure creatinine kinase if indicated.
- Warfarin – statin may increase the INR and risk of bleeding; adjust warfarin dose according to INR.

Potential adverse effects:

- Common – myalgia, mild transient gastrointestinal symptoms, headache, insomnia, dizziness
- Rare – myopathy (with or without creatinine kinase elevation), rhabdomyolysis, renal failure, hepatitis, liver failure, alopecia, paraesthesia, peripheral neuropathy, impotence, nightmares, gynaecomastia, hypersensitivity, anaphylaxis, angioedema, toxic epidermal necrolysis, delayed wound healing
- Other – minor transient increases in transaminase and creatinine kinase are commonly found in the first weeks of treatment and appear to be dose related.

If there is any suspected side effect, or a clinical need to place your patient on a statin, or any of the medications mentioned above, we would very much appreciate you first contacting our chief investigator [name], or [name] on [name] before starting. Thank you for your cooperation.

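### No entry criterion, deferral rule or dose rule covers a person already taking cyclosporin, clarithromycin, erythromycin, itraconazole or ketoconazole, although Appendix 9 warns against full-dose simvastatin with each of them

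*Protocol*

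**What the plan says.** **Entry rules.** Three criteria in Protocol sections 6.2 and 6.3 bear on drugs or on statin safety:

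- Inclusion 6 keeps out anyone now taking a cholesterol-lowering drug.
- Exclusion 2 concerns drugs that may affect vision, with plaquenil, chloroquine and major tranquilizers as examples.
- Exclusion 4 is headed "4) Statins is clinically contraindicated", followed by allergy, ALT above twice the upper limit of normal, and a past severe reaction to a statin.

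**Dose.** Section 7 gives simvastatin 40 mg or placebo. Section 5 keeps each participant on the same treatment throughout. Section 8.5 starts treatment once the baseline assessments are complete.

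**Interactions.** Appendix 9, the letter to the GP, lists drug interactions. For cyclosporin it says "increases risk of myopathy or rhabdomyolysis; use lowest effective statin dose, monitor for adverse effects, and measure creatinine kinase if indicated". For clarithromycin, itraconazole, ketoconazole and erythromycin it names the same risk and says "stop statin temporarily, for the duration of antimicrobial treatment".

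**Medication list.** Section 8.4 and Appendix 10 have prescription and over-the-counter medicines recorded at the initial visit.

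**The concern.** The letter to the GP treats full-dose simvastatin with any of these five drugs as something to avoid or modify. The entry rules do not carry that over. Someone on long-term cyclosporin, or part-way through a course of one of the antimicrobials, can meet every written criterion and be given 40 mg.

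The harm at stake is one that the protocol itself names: Appendix 9 lists myopathy, rhabdomyolysis and renal failure among rare adverse effects. Section 1 says that participants have cholesterol below the level at which treatment is normally recommended, so no lipid indication offsets an avoidable interaction. Eligibility is fixed in the protocol, so this is not a detail that would ordinarily wait for a statistical analysis plan.

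**Working it through.** No sample size, power or event figure is involved. The check compares the interaction list in Appendix 9 with the entry criteria.

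**Step 1. Which interactions are left open at entry?**

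| Appendix 9 entry | Dealt with at entry? |
|---|---|
| Bile acid resins | Yes, inclusion 6 |
| Gemfibrozil | Yes, inclusion 6 |
| Nicotinic acid, lipid-lowering doses | Yes, inclusion 6 |
| Warfarin | No entry rule, but the advice adjusts warfarin, not the statin |
| Clarithromycin, itraconazole, ketoconazole, erythromycin | No |
| Cyclosporin | No |

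Of 6 entries, 3 are barred by inclusion 6 and 1 does not call for a change to the statin: 6 − 3 − 1 = 2 entries remain. They name 4 + 1 = 5 drugs. Named in an inclusion or exclusion criterion: 0 of 5.

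**Step 2. Is there another rule before the first dose?** Section 8.2 describes pre-visit contact with blood tests and questions on cardiovascular disease and risk factors. It describes no check for interacting drugs. The medication list is taken at the initial visit, where Appendix 10 also places randomisation, and section 8.5 gives treatment only after baseline assessments. The information is therefore available in time, but no section says what to do with it. No section defers the start, and none allows a lower dose.

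**Step 3. Do the letters work as an entry check?** Both are issued on commencing medication. Appendix 9 opens "Your patient has been enrolled into the Age-Related Maculopathy Statins Study (ARMSS". Its request to telephone first covers "a clinical need to place your patient on a statin, or any of the medications mentioned above", which describes a drug about to be started. Appendix 8 asks the participant to remind the doctor, "especially when he is about to prescribe any drug (particularly antibiotics), as there are a few but important interactions", and this also looks ahead. The antimicrobial advice in Appendix 9 is not limited to new prescriptions, so a GP who reads it during a course could stop the tablets. That would come after the start of treatment, and it depends on the participant delivering the letter.

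**Step 4. What applies after the first dose?** Appendix 8 tells participants to "seek medical advice promptly if you experience muscle pain, tenderness or weakness, dark urine". Section 11.4 has staff ask about muscle soreness at each visit (Appendix 10 places the first at 1 month), encourages participants to report problems as they arise, repeats blood and liver tests after 4 weeks, and appoints a Safety Officer. Appendix 9 also asks for a call about any suspected side effect. The blood panel in section 8.4 lists no creatine kinase; for cyclosporin, Appendix 9 leaves that test to the GP. These measures can detect or limit harm. They do not prevent the exposure from starting.

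**The case against.** The strongest reply is that a rule already exists. The heading of exclusion 4 is general, nothing says that its three items are exhaustive, and the clinician has the medication list before dispensing. This stands in part: a careful investigator can exclude such a person. But Appendix 9 presents the five drugs as interactions to manage, not as contraindications, so two investigators could reasonably decide differently under the same heading.

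A second reply is that excluding cyclosporin users goes further than Appendix 9, which allows co-use at a reduced dose with monitoring. That is fair, and a written management rule would also close the gap. The protocol has no such rule and describes no lower dose. Exclusion is the simpler choice.

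A third reply is that an antimicrobial course is short and that the letters and section 11.4 cover most of what follows. This limits the size of the problem but does not remove it.

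Two stronger readings should be resisted:

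- **Half of current users would receive simvastatin.** A reader might infer this from the 1:1 allocation. It ignores discretion under exclusion 4. If a fraction p of current users is randomised despite that discretion, the expected share starting simvastatin is p × 1/2, anywhere from 0 to one half as p runs from 0 to 1. The documents do not give p.
- **The dose could be lowered within the trial.** Appendix 8 says "Take two tablets in the evening with food", and a reader might infer that one tablet would be half the dose. Section 7 gives 40 mg per tablet, so one tablet would still be 40 mg. The tablet count is a separate discrepancy, and nothing here rests on it.

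**Conclusion.** The point holds as a gap in the written entry rules. None of the five drugs is named, and no deferral or dose-reduction rule covers a person already taking one. Such a person could be started on a combination that the protocol's own letter says to modify or avoid.

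The number of people concerned is not stated and is probably small. The discretionary heading, the medication list, the letters and the provisions of section 11.4 reduce the risk without reliably closing the gap. This is a safety point only: the documents give no basis for claiming bias between arms or an effect on power. The conclusion rests on the text available. The consent form and participant information (Appendices 4 and 5) are not in it, so any warning there cannot be checked. The amendment is worth making because the named harm is serious and the remedy is cheap.

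**What to change.** - Add to exclusion 4 in section 6.3: current cyclosporin, and long-term use of clarithromycin, erythromycin, itraconazole or ketoconazole.
- For a short course of any of the four antimicrobials, defer randomisation or the first dose until the course has ended.
- In section 8.5, require that the medication list from the initial visit be checked against these five drugs before a medication number is issued.

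The cost is a short protocol amendment. The list is already collected, so no new procedure is needed. A few otherwise eligible people would be excluded or would start later.

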## **7. STUDY MEDICATIONS**

**Dose:** The medication involved in this study are either SIMVASTATIN at 40mg per tablet or a PLACEBO.

Both are supplied by Merck Sharp & Dolme Pty Ltd.

**Administration:** Patients receive their study medication following the completion of their baseline assessment.

Unused tablets and empty jars are requested to be returned to the study centre for assessment of compliance.

